# Designing and Evaluating a Personalized, Human-Centered Dietary Decision Support System for Use Among People With Diabetes in an Indian Setting: Protocol for a Quasi-Experimental Study

**DOI:** 10.2196/13635

**Published:** 2022-03-08

**Keywords:** type 2 diabetes, diabetes management, dietary decision support, diet record, India

## Abstract

**Background:**

Human-centered dietary decision support systems are fundamental to diabetes management, and they address the limitations of existing diet management systems.

**Objective:**

The objective of the proposed study is to evaluate the use of an interactive, telephone-linked, personalized, human-centered decision support system for facilitating the delivery of personalized nutrition care for patients with diabetes.

**Methods:**

A quasi-experimental trial was conducted between the period of June and December 2018. Study participants were recruited from Community Health Center, Dharamshala, Kangra (urban population), and Model Rural Health Unit, Haroli Block, Una (rural population). Eligible participants included adults aged ≥30 years with controlled or uncontrolled diabetes, those who agreed to participate in the study, those who were available for follow-up interviews, and those with a telephone or computer at home. Diabetic status was determined via a physician’s diagnosis. Individuals with mental or physical challenges that affected their ability to use an electronic diet record, those who were not available for a telephone follow-up, and those who were involved in other protocols related to dietary assessments were excluded. The study participants were randomized into the following two groups: the intervention group (telephone-linked dietary decision support system) and the control group (paper-based diet record). Study participants in the intervention group recorded their daily dietary intake by using a telephone-linked, personalized, human-centered dietary decision support system and received personalized feedback and diet education via SMS text messaging. Study participants in the control group were provided with only a paper-based diet record for documenting their daily dietary intake. Follow-up visits were conducted at 3 and 6 months from the baseline in both groups. Differences in diabetes knowledge, attitudes, and practices will be measured across groups.

**Results:**

The collection of baseline data from 800 study participants in both the intervention (n=400) and control groups (n=400), which were stratified by urban (control group: n=200; intervention group: n=200) and rural settings (control group: n=200; intervention group: n=200), has been completed. Follow-up data collection for months 3 and 6 is ongoing and is expected to be completed by October 2019.

**Conclusions:**

We anticipate that the intervention group will show significant changes in nutrition knowledge, attitudes, and practices; satisfaction with care; and overall diabetes management. We also expect to see urban-rural differences across the groups. The uniqueness of our nutrient data capture process is demonstrated by its cultural and contextually relevant features—diet capture in both English and Hindi, diet conversion into caloric components, sustained diet data collection and participant adherence through telephone-linked care, and auto-generated reminders.

**International Registered Report Identifier (IRRID):**

DERR1-10.2196/13635

## Introduction

Type 2 diabetes (T2D) is a rapidly growing chronic health problem, and the complications of T2D cause significant morbidity and mortality. Globally, 415 million people are living with T2D mellitus, and this is estimated to increase to 642 million people by 2040 [1]. The proliferation of T2D is the most notable in low- and middle-income countries, and this has been attributed to a number of factors, including an aging population, population growth, urbanization, the increasing prevalence of obesity, and physical inactivity [2-5]. India, China, and the United States have the highest diabetes incidence rates globally. According to the International Diabetes Federation estimates, the number of patients with diabetes in India is projected to increase to approximately 70 million by 2025—almost double the amount from 2007 [1].

A key outcome of proper diabetes management is the development of healthy eating patterns [3]. In addition, daily physical activity sessions are recommended to regulate blood glycemic levels. [4]. Proper glycemic control is critical to the prevention or delay of the onset of acute and chronic complications and to the improvement of quality of life among people with diabetes. Providing self-management education and support tools to improve diabetes knowledge, foster treatment adherence, promote lifestyle changes, and enable the self-monitoring of blood glucose is fundamental to this process [5,6].

Dietary intake assessment is a fundamental step in developing interventions for people living with T2D [6]. Dietary intake has been measured by using a variety of methods in the existing literature, including dietary recalls, weighed diet records, diet history reports, and food frequency questionnaires [6-8]. None of these methods have demonstrated adequate accuracy and reliability in determining food intake. A variety of technology-based applications have also been developed for estimating and recording food consumption, but significant limitations have been reported, including small sample sizes, insufficient outcome evaluation periods, high costs, and inappropriate message framing [9,10]. Future studies using randomized controlled trial designs, larger sample sizes, and longer durations of evaluation are recommended to establish the intervention capabilities of technology-based diet interventions [10-14].

The objective of the proposed study is to evaluate the use of an interactive, telephone-linked, personalized, human-centered decision support system for facilitating the delivery of personalized nutrition care for patients with diabetes. To the best of our knowledge, this is the first study to design and develop an intervention model after assessing the needs of users from urban and rural settings in an Indian context. The proposed study has three specific aims, as follows:

Examine and compare the factors that influence the intake of a healthy diet among people with diabetes living in the urban and rural settings of Himachal PradeshIdentify the necessary components of the personalized, human-centered dietary decision support system that can gather, analyze, and provide individualized dietary feedbackCompare the effectiveness of the personalized, human-centered dietary decision support system to that of other paper-based methods of diet recording for documenting nutrient intake among people with diabetes

## Methods

### Ethics Approval

Ethical approval was obtained from the Institutional Review Board of [name] Medical College Kangra (institutional review board number: 116/2016).

### Study Design

A quasi-experimental trial was conducted between the period of June and December 2018 (Figure 1). Study participants were recruited from the following two urban and rural locations: Community Health Center, Dharamshala, Kangra (urban population), and Model Rural Health Unit, Haroli Block, Una (rural population). Eligible study participants included (1) adults aged ≥30 years, (2) those with controlled or uncontrolled diabetes, (3) those who agreed to participate in the study, (4) those who were available for follow-up interviews, and (5) those with a telephone or computer at home. Diabetic status was based on a physician-confirmed diagnosis of diabetes and the prescription of medications for diabetes management. The exclusion criteria comprised the following: (1) the presence of any mental or physical challenge affecting the study participants’ ability to use an electronic diet record, (2) unavailability for a telephone follow-up, and (3) involvement in other clinical trials or protocols related to dietary assessments. The study was funded by the Indian Council of Medical Research.

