### Study Groups

The study participants were randomly assigned into the following two groups: the intervention group (telephone-linked dietary decision support system) and the control group (paper-based diet record; Figure 1). The randomization was conducted following the assessment of participants’ eligibility for inclusion in the study. Study participants in the intervention group (group 1) recorded their daily dietary intake by using a telephone-linked, personalized, human-centered dietary decision support system and received personalized feedback and diet education via SMS text messaging. The personalized, human-centered dietary decision support system is a telephone-linked decision support system designed to provide tailored dietary education to patients with diabetes. The study participants were able to access the personalized, human-centered dietary decision support system through their computers, cell phones, or a telephone-linked service, depending on the technology platform available to them. The telephone-linked service enabled the participants (including those who did not have a technology platform to access the personalized, human-centered dietary decision support system) to receive phone calls from our research team in order to record their daily dietary intake. The personalized, human-centered dietary decision support system also generated automatic alerts that served as reminders to the participants who had not reported their daily diet intake. Study participants in the control group were provided with a paper-based diet record for documenting their daily dietary intake. Both the intervention group and control group were provided with a diabetes educational booklet at baseline. However, the study participants in the control group were also provided with a booklet to document their diet log on a daily basis. Follow-up visits were conducted at 3 and 6 months from the baseline in both groups. Baseline data were gathered on sociodemographics; health literacy; physical activity; anthropometric measurements; blood sugar testing; and diabetes knowledge, attitudes, and practices (KAPs). Follow-up data were gathered on anthropometric measurements, diabetes KAPs, blood sugar testing, and satisfaction with medical care.

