### Statistical Analysis

Baseline characteristics will be summarized and stratified by intervention group. The primary outcomes—adherence to dietary guidelines, KAPs, and patient satisfaction with medical care—will be compared between groups by using a log-rank test. A Cox proportional hazards regression model will be used to adjust for confounders that differ significantly between the two groups at the .20 level of significance. A generalized linear mixed model using a binomial distribution and logit link function will be used to examine the binary secondary objective—subjects’ satisfaction with medical care. The group types (ie, the intervention and control groups) will be used as a fixed effect, and subject data will be used as random effects. This will be done by using a variance components covariance structure. To adjust for confounders that differ significantly between the two groups at the .20 level of significance, covariates will be added to the model, and a linear regression model will be used.

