## Results

Data collection was conducted between the period of June and December 2018. The collection of baseline data from 800 study participants in both the intervention (n=400) and control groups (n=400), which were stratified by urban (control group: n=200; intervention group: n=200) and rural settings (control group: n=200; intervention group n=200), has been completed. Follow-up data collection for months 3 and 6 is ongoing. We expect the follow-up data collection to be completed by October 2019. We are currently analyzing the baseline data and generating reports, which will be presented in our upcoming manuscript.

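### The study is labelled quasi-experimental yet says participants were randomized, leaving the strength of the causal claim and the right covariate adjustment ambiguous

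*Protocol article*

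**What the plan says.** The title ends "Protocol for a Quasi-Experimental Study", and the abstract and the Study Design section both state "A quasi-experimental trial was conducted between the period of June and December 2018".

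The abstract's Methods paragraph then says "The study participants were randomized into the following two groups". The Study Groups section says "The study participants were randomly assigned into the following two groups" and gives the timing: "The randomization was conducted following the assessment of" eligibility. The abstract therefore carries both descriptions in one paragraph.

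The Results section reports 400 participants per arm, "stratified by urban (control group: n=200; intervention group: n=200) and rural settings", with 200 per arm in each setting.

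The Statistical Analysis section gives a single plan. The primary outcomes "will be compared between groups by using a log-rank test", and models are then used to "adjust for confounders that differ significantly between the two groups at the .20 level of significance". The same .20 rule is repeated at the end of that section for a linear regression model.

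The third specific aim in the Introduction is a comparison of effectiveness against paper-based recording. The Discussion expects higher satisfaction in the intervention group and attributes this to features of the system.

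**The concern.** In ordinary usage a quasi-experiment assigns treatment without randomization, so the label and the allocation statements cannot both be taken at face value.

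Allocation determines what the third aim can support. With random assignment, a difference between arms can be attributed to the intervention, subject to the usual conditions on follow-up and measurement. Without it, the same difference carries a causal reading only as far as the adjustment removes confounding. The Introduction itself asks for randomized controlled designs to establish what technology-based diet interventions can do, so the authors treat the distinction as important. As the article stands, a reader or evidence synthesist cannot tell which class of study this is.

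The adjustment also has to match the allocation, and the .20 screen serves neither case well.

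**Working it through.** The plan gives no figure on this point, so the main check sets the statements side by side.

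**Step 1. Label against allocation.**
- Quasi-experimental: title, abstract, Study Design.
- Randomized or randomly assigned: abstract, Study Groups.
- Allocation after the eligibility assessment: Study Groups only.

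**Step 2. Can both stand?** They could if the article said, for example, that assignment was by alternation, or that the label refers only to the urban-rural comparison, which cannot be randomized. It says neither. Allocation of whole sites does not fit the counts, because each setting contains both arms at 200:200. Equal counts do not prove randomization either, since alternation or quotas would give the same numbers.

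**Step 3. Does the plan depend on the label?** No. The log-rank test, the Cox model, the mixed model and the linear regression are stated without reference to how participants were allocated.

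**Step 4. The .20 screen if allocation was random.** Any baseline difference is then due to chance, so each candidate covariate is selected with probability 0.20. The article does not list the candidates, so their number k is an assumption, shown over a range.
- Expected number selected = 0.20 × k: 1 for k = 5, 2 for k = 10, 3 for k = 15.
- Chance that at least one is selected = 1 − 0.8^k, if independent: 0.67, 0.89 and 0.96.

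The adjusted model is thus chosen by chance imbalance. Baseline KAP, a natural predictor of follow-up KAP, would if listed as a candidate be left out with probability 0.80. Setting has a between-arm difference of exactly zero at baseline (200/400 against 200/400), so the screen cannot select it there, although the article expects urban-rural differences.

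**Step 5. The .20 screen if allocation was not random.** The two-sided .20 cutoff is z = 1.28. A standardized covariate is selected when its observed difference exceeds 1.28 × √(2/n).
- n = 400 per arm: 1.28 × 0.0707 = 0.09 SD.
- n = 200 per arm (one setting): 1.28 × 0.1 = 0.128 SD.

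Only the imbalance and the sample size enter this rule. The covariate's relation to the outcome, which also determines confounding, does not. A strong predictor just under the threshold is dropped and an irrelevant variable just over it is kept. Unmeasured confounders are outside its reach altogether.

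**The case against.** The strongest reply is that this is a mislabel and no more. The operational text points one way: Study Groups describes random assignment and says when it took place, the abstract agrees, and the 1:1 counts in each setting are consistent with it. Figure 1, cited in both Study Design and Study Groups, is not shown, and neither is the full protocol. Allocation detail may well be there, and its absence from the article is not a fault. All this stands. It still leaves the title and the Study Groups section in conflict in the published text.

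A second reply is that the .20 screen is a separate weakness. That is largely right. The Statistical Analysis section never ties the screen to a design, so nothing shows that the label led to it. It belongs here only because correcting the design statement requires the adjustment to be matched to it.

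Three stronger readings are tempting and are not supported:
- *A reader might infer that the trial's conclusion is undefined.* The arms, outcomes and analysis plan are stated and do not change with the label. If allocation was random, the label is a misnomer; if not, the inference is weaker but still defined.
- *A reader might attach a bias to the non-random case.* For example, an assumed imbalance of 0.3 SD and an assumed correlation of 0.5 with the outcome give 0.3 × 0.5 = 0.15 SD, against a planned effect of 0.2/0.7 = 0.286 SD. Both inputs are invented, and the result is an unadjusted bias. With 400 per arm, a measured covariate shifted by 0.3 SD has expected z = 0.3/√(2/400) = 4.24, so the screen would select it with probability Φ(4.24 − 1.28) = Φ(2.96), about 99.8%. With 200 per arm, z = 3.0 and Φ(1.72) is about 96%. The figure could apply only to an unmeasured confounder, for which the article gives no basis.
- *A reader might infer that randomization was stratified by setting.* The Results section describes the baseline sample as stratified. It does not say that the random sequence was.

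**Conclusion.** The point holds as an unreconciled contradiction about how participants were allocated, together with an adjustment rule that fits neither description. It should be corrected.

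Its size is qualitative. It bears on the causal reading of every between-group comparison, but no bias in any result has been shown, and the documents do not reveal which description is correct. The selection figures for the screen assume 5 to 15 candidate covariates and, for the chance of at least one selection, independence between them. The contradiction itself rests on no assumption beyond the usual meaning of quasi-experimental.

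**What to change.** State in one sentence how participants were allocated, and use one matching design label in the title, abstract, Study Design and Study Groups.

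In Statistical Analysis, delete both uses of the .20 between-group screen and name a prespecified covariate set, chosen without reference to observed group differences:
- **If allocation was random:** call the study a randomized trial and adjust for baseline KAP and setting. Describe the randomization as stratified by setting only if the sponsor confirms that it was.
- **If allocation was not random:** remove the statements that participants were randomized or randomly assigned. Adjust for a fixed list of measured confounders chosen on subject-matter grounds: baseline KAP, age, education, health literacy, computer and internet use, and blood sugar. Word the conclusions with the caution that unmeasured confounding could remain.

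The sponsor knows which case applies. All the listed variables are already collected at baseline, so the cost is rewording and a short covariate list, with no new data.

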**Figure 1 figure1:**
[figure not shown]
Study participant recruitment.

### Study Groups

The study participants were randomly assigned into the following two groups: the intervention group (telephone-linked dietary decision support system) and the control group (paper-based diet record; Figure 1). The randomization was conducted following the assessment of participants’ eligibility for inclusion in the study. Study participants in the intervention group (group 1) recorded their daily dietary intake by using a telephone-linked, personalized, human-centered dietary decision support system and received personalized feedback and diet education via SMS text messaging. The personalized, human-centered dietary decision support system is a telephone-linked decision support system designed to provide tailored dietary education to patients with diabetes. The study participants were able to access the personalized, human-centered dietary decision support system through their computers, cell phones, or a telephone-linked service, depending on the technology platform available to them. The telephone-linked service enabled the participants (including those who did not have a technology platform to access the personalized, human-centered dietary decision support system) to receive phone calls from our research team in order to record their daily dietary intake. The personalized, human-centered dietary decision support system also generated automatic alerts that served as reminders to the participants who had not reported their daily diet intake. Study participants in the control group were provided with a paper-based diet record for documenting their daily dietary intake. Both the intervention group and control group were provided with a diabetes educational booklet at baseline. However, the study participants in the control group were also provided with a booklet to document their diet log on a daily basis. Follow-up visits were conducted at 3 and 6 months from the baseline in both groups. Baseline data were gathered on sociodemographics; health literacy; physical activity; anthropometric measurements; blood sugar testing; and diabetes knowledge, attitudes, and practices (KAPs). Follow-up data were gathered on anthropometric measurements, diabetes KAPs, blood sugar testing, and satisfaction with medical care.

### Intervention Development

A telephone-based, personalized, human-centered dietary decision support system for populations with diabetes was designed to provide tailored dietary education to patients with diabetes (Figure 2). A human-centered approach was used in the design process. Human-centered design principles require end users to be prioritized in intervention design and development [15]. User characteristics, needs, and preferences are vital for ensuring the optimal use of technology-enabled interventions [15] (Figure 3). The failure to fully implement human-centered design in dietary intervention designs has been a limitation in prior studies [11]. The personalized, human-centered dietary decision support system is comprised of the following components: (1) the electronic monitoring of diet records, (2) personalized dietary and disease feedback, (3) the nutrient calculation of daily diet intake per meal, and (4) alerts and reminders (Figure 4).

The personalized, human-centered dietary decision support system can be used on cell phones, PDAs, and computers, depending on the technology platforms available to users across various Indian settings. Dietary information from the prospective users was gathered on a daily basis. This information included the various food sources consumed and the quantity and timing of food consumption. A nutrient database of food choices and their caloric values was subsequently created [16]. This nutrient database included the following components: food type, food class, quantity, and calorie estimation. A message library in both the English and Hindi languages (a local Indian dialect) was prepared, so that individuals could be sent weekly messages on how best to manage their diet. Based on the study participants’ dietary intake, interactive tailored feedback was provided (Figure 5). Study participants also received auto-generated reminders and alerts if their dietary information was not received as scheduled.

